## Abstract

**Background::**

Recently, trimethylamine N-oxide (TMAO) unexplained gut microbe has been proposed as a promising risk factor for atherosclerotic cardiovascular disease (CVD) pathogenesis and adverse events. The relationship of TMAO with coronary atherosclerotic burden has been evaluated in patients with stable coronary artery disease and ST-segment elevation myocardial infarction, but still needs to be explored in newly diagnosed non-ST-segment elevation myocardial infarction (NSTEMI) patients.

**Material and methods::**

A prospective, single-center, SZ-NSTEMI trial (ChiCTR1900022366) is underway to investigate the relationship of TMAO with the severity and prognosis of coronary atherosclerosis in newly diagnosed NSTEMI patients who will undergo coronary angiography with primary percutaneous coronary intervention (pPCI). The primary endpoint of the study will be assessed the association of TMAO with coronary atherosclerotic severity quantify by the number of diseased coronary arteries and SYNTAX score after the coronary angiography. The secondary endpoints will be identified the TMAO as a prognostic biomarker for the short (1 month) and long-term (12 months) major cardiovascular and cerebrovascular events (MACCEs) rate including myocardial infarction, target vessel revascularization, stroke, heart failure, all-cause rehospitalization, and all-cause mortality after the pPCI. The blood samples will be collected from each patient before the procedure to measure the TMAO by isotope dilution high-performance liquid chromatography. In conclusion, SZ-NSTEMI will be the first cohort that will be investigated the association of TMAO with the severity and prognosis of coronary atherosclerotic burden in NSTEMI patients, aiming to identify TMAO as a predictor and a prognostic biomarker.

## Introduction

1

### Background and rationale

1.1

Cardiovascular disease (CVD) is associated with a markedly high incidence in the general population and considered the leading cause of death worldwide.^[1–3]^ Non-ST-segment elevation myocardial infarction (NSTEMI) is the most frequent type of CVD and represents the largest group of patients undergoing primary percutaneous coronary intervention (pPCI).^[1–3]^ Though NSTEMI patients may have lower in-hospital mortality than patients with ST-segment elevation myocardial infarction (STEMI), but long-term mortality is two-fold higher than that in patients with STEMI.^[4,5]^ Moreover, sufficient attention has been given to traditional risk factors, such as age, gender, hypertension, dyslipidemia, smoking, and diabetes, and considerable use of modern therapies only decreased 30% of CVD related mortality and morbidity.^[1–3,6]^ The early risk stratification and optimal treatment strategies are crucial for improving the prognosis of NSTEMI patients. Therefore, an increased demand to explore new CVD pathogenesis risk factors that have not been explained yet in clinical settings.

Recently, plasma the trimethylamine N-oxide (TMAO) unexplained gut microbe has emerged as a promising risk factor for CVD pathogenesis and adverse events.^[7–13]^ The trimethyllysine (TML) a precursor of TMAO was also found both alone and in combination with TMAO an independent and reproducible clinical predictor for the incidence of mortality in CVD patients.^[14]^ TMAO was recently shown to be an independent predictor of a high atherosclerotic burden in patients with STEMI and stable coronary artery disease.^[15,16]^ However, the association of TMAO and TML yet to be investigated in NSTEMI patients. Here, we present the study protocol of the SZ-NSTEMI trial, a prospective, single-center, cohort study which aimed to investigate the relationship of plasma TMAO and TML with an atherosclerotic burden and major cardiovascular and cerebrovascular events (MACCEs) including myocardial infarction, target vessel revascularization, stroke, heart failure, all-cause re-hospitalization, and all-cause mortality after CAG with pPCI in NSTEMI patients.

### Study objective

1.2

The primary objective of the study is to evaluate the relationship between TMAO and TML levels with the extent of an atherosclerotic burden as quantified by the number of diseased coronary vessels and the SYNTAX score in NSTEMI patients.

The secondary objective of the study is to assess TMAO and TML as prognostic biomarkers for the short (1 month) and long-term (12 months) MACCE rate after the pPCI in NSTEMI patients.

## Methods/design

2

### Study design

2.1

This clinical prospective, non-randomized SZ-NSTEMI trial (ChiCTR1900022366) is underway to investigate the relationship of plasma TMAO and TML levels with an atherosclerotic burden and MACCE rate in NSTEMI patients. The study protocol was approved by the Ethics Committee of Fuwai Hospital Chinese Academy of Medical Sciences, Shenzhen (Ethics approval number: YN201901) and registered clinical trial (ChiCTR1900022366). All study procedures comply with the Declaration of Helsinki and all participants will give informed consent after screening inclusion and exclusion criteria before enrollment. The duration of the study is two years which include the selection, initial screen, CAG, pPCI, and the follow-up period for the MACCEs after the pPCI.

### Study population

2.2

The present work will be enrolled 2 groups of individuals including Study group (200 newly diagnosed NSTEMI patients and having at least single or multiple coronary lesions ≥ 70% after CAG to fulfill eligibility for pPCI) and Control group (100 healthy individuals) at Fuwai Hospital. The Study group already enrolled 70 NSTEMI patients and will be continued to complete the enrollment of 200 patients who will undergo CAG with pPCI. The NSTEMI will be diagnosed according to symptoms, electrocardiogram (ECG) changes and myocardial enzyme results as recommended by European Society of cardiology.^[1–3]^ NSTEMI symptoms will be noted as the presence of acute chest pain or chest tightness or dyspnea with duration over 30 minutes but no persistent ST-segment elevation; ECG changes may include ST-segment depression ≥0.05 mV, T-wave inversion ≥0.3 mV or flat T wave, or transient ST-segment elevation ≤0.05 mV or maybe normal ECG; and myocardial enzyme with positive elevated troponin T and I, and/or CK-MB exceeding the upper limit of the normal range.^[1–3]^ The Control group will be included 100 healthy individuals without known cardiovascular disease or/and non-cardiovascular diseases who will only visit for health screen. The Control group purpose will be provided the reference interval values for TMAO and TML levels compared to the Study group with a ratio of 1:2 respectively.

The study will be conducted over a period of 2 years in which all included individuals will be examined at baseline and Study Group individuals will be followed up for the short (1 month) and long-term (12 months) MACCE rate after the pPCI, as shown by SZ-NSTEMI diagram with a flowchart that will be used in the present study (Fig. 1).

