**Figure 1 F1:**
[figure not shown]
Flow chart diagram of the SZ-NSTEMI study protocol. B/W = between, CAG = coronary angiography, ECG = electrogram, M = month, MACCE = major adverse cardiovascular and cerebrovascular event, MVD = multiple vessels disease, NSTEMI = non ST-segment myocardial infarction, pPCI = primary percutaneous coronary intervention, SVD = single vessel disease, TMAO = trimethylamine N-oxide, TML = trimethyllysine.

Inclusion criteria:

1.Newly diagnosed NSTEMI patients without having previous coronary artery disease2.Having at least single or multiple coronary lesions ≥70% after CAG to fulfill eligibility for pPCI3.Willing to provide informed consent4.Both men and women aged between 18 and 75 years old.

Exclusion criteria

1.Patients with a previous history of coronary artery disease including STEMI, NSTEMI, stable or unstable coronary artery disease or percutaneous transluminal coronary angioplasty or PCI or coronary artery bypass surgery2.Having single coronary lesion < 70% or patient not willing to perform pPCI with single coronary lesion ≥ 70%.3.Having left main coronary artery lesion4.Patients present with diagnosis of STEMI, stable or unstable coronary artery disease5.Patients with severe valvular Heart disease, severe renal and hepatic disease, heart failure, peripheral arterial disease, atrial fibrillation, chronic obstructive lung disease, acute and chronic infection, history of cancer, and history stroke or bleeding within 3 months.6.Patient unwillingness to participate and not willing to provide informed consent7.Pregnancy or lactation8.Conditions related to an estimated life expectancy of less than 1 year.

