### Sample size

2.9

The protocol planned to enroll 300 participants including 200 NSTEMI patients in the Study group and 100 healthy individuals in the Control group. The ratio of 2:1 sample size will provide 80% power to detect an absolute difference of TMAO and TML biomarkers between the 2 groups. The 200 NSTEMI patients with given a 10% rate of loss during follow-up for MACCEs as secondary endpoints will provide 80% power at a two-sided significance level of 0.05.

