### Statistical analysis

2.10

Continuous variables will be expressed as mean ± standard deviation or median with interquartile range, whereas categorical data will be expressed as percentages. Continuous variables will be analyzed using *t* tests or Fisher exact or Pearson χ^2^ tests for categorical variables as appropriate. Kolmogorov-Smirnov test will be performed for normality. Pearson and Spearman correlation analyses will be used to examine the correlations between TMAO and TML levels, SYNTAX score and the numbers of diseased coronary vessels. Ordinal logistic regression analyses with adjustments for traditional risk factors (including age, sex, hypertension, diabetes mellitus, smoking, low-density lipoprotein cholesterol level, high-density lipoprotein cholesterol level, and triglyceride and body mass index) will be used to determine the association of TMAO and TML with a high SYNTAX score and the presence of multiple vessel diseases. Kaplan-Meier curves will be used for correlation of TMAO and TML with the short and long-term MACCE rate after the pPCI. A *P* value ≤ .05 will be considered statistically significant. All statistical analyses will be performed with SPSS 25 (IBM).

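### The NSTEMI versus healthy-control comparison of TMAO and TML carries an 80% power claim but no stated matching or adjustment, so it is open to confounding by age, sex and renal function

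*Protocol article*

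**What the plan says.** **Controls.** Section 2.2 defines them as "100 healthy individuals without known cardiovascular disease or/and non-cardiovascular diseases who will only visit for health screen". No sex distribution or matching is given. The age limit, "Both men and women aged between 18 and 75 years old", stands in an inclusion list whose other disease-specific items are written for NSTEMI patients.

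**Their purpose.** Section 2.2 states it, with one control for every two patients: "The Control group purpose will be provided the reference interval values for TMAO and TML levels compared to the Study group with a ratio of". Section 2.9 goes beyond reference values: "The ratio of 2:1 sample size will provide 80% power to detect an absolute difference of TMAO and TML biomarkers between the 2 groups". No mean difference or SD accompanies that figure.

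**The other power claim.** Section 2.9 makes a second one for the 200 patients, allowing for losses: "10% rate of loss during follow-up for MACCEs as secondary endpoints will provide 80% power at a two-sided significance level of 0.05".

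**Analysis.** Section 2.10 says "Continuous variables will be analyzed using" t tests, without covariates. It then specifies ordinal logistic regression adjusted for age, sex, body mass index, hypertension, diabetes, smoking and lipids, but only for a high SYNTAX score and multivessel disease.

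**Endpoints.** Sections 1.2 and 2.6 make the association with SYNTAX score and number of diseased vessels primary, and MACCE prognosis secondary. The comparison with healthy controls is in neither list.

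**The concern.** Controls chosen for being free of known disease, from people attending a health screen, can differ from NSTEMI patients in more than the infarction. By adjusting its other models for age, sex and body mass index, the protocol already treats these as confounders. It does not carry that adjustment over to the group contrast.

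Renal function can differ by design. Patients are excluded only for severe renal disease, so milder impairment is allowed, while controls may have no known non-cardiovascular disease. The Discussion itself links TMAO to chronic kidney disease, yet renal function is not among the covariates in section 2.10.

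At stake is the reading of the group difference. A significant t test could reflect age, sex or kidney function rather than NSTEMI. Reference values from these controls might also fit the patients' age range poorly.

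**Working it through.** **Inputs from the protocol.** 200 patients and 100 controls (section 2.9); 80% power for the group difference (section 2.9); significance threshold 0.05 (section 2.10). Two-sided testing is stated only for the MACCE claim and is assumed here for the group contrast.

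**Step 1: the plan's own figure.** The 80% cannot be reproduced, because no difference or SD is given. It can be solved for the detectable standardised difference d:

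- SE = √(1/100 + 1/200) = √0.015 = 0.1225 SD
- d = (1.960 + 0.842) × 0.1225 = 0.343 SD

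So 200 v 100 gives 80% power at 0.343 SD for an unadjusted comparison.

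**Step 2: false rejection under imbalance.** Suppose the true disease difference is zero, but covariate imbalance shifts the group means by b SD. The unadjusted test rejects with probability Φ(b/SE − 1.96) + Φ(−b/SE − 1.96). The values of b are assumptions, since the protocol gives no age or sex distribution and no slope of either marker on age.

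| Assumed shift b (SD) | b/SE | Rejection rate |
|---|---|---|
| 0 | 0 | 5.0% |
| 0.05 | 0.41 | 6.9% |
| 0.10 | 0.82 | 12.9% |
| 0.20 | 1.63 | 37.2% |
| 0.30 | 2.45 | 68.8% |

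For example, a marker slope of 0.2 SD per SD of age with a 1 SD age gap gives b = 0.2 × 1 = 0.20 and 37.2%. All of these shifts are smaller than the 0.343 SD that the design can detect with 80% power.

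**Step 3: cost of adjusting for age.** With p = 2/3 of participants in the study group and an age gap of g within-group SDs, the variance of the group effect is inflated by 1 + p(1 − p)g² = 1 + 0.222g². The detectable difference is multiplied by the square root of this. Any residual variance that age explains is ignored.

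| Assumed gap g | Inflation | Detectable difference at 80% | Power at 0.343 SD |
|---|---|---|---|
| 0 | 1.000 | 0.343 SD | 80.0% |
| 0.5 | 1.056 | 0.353 SD | 77.8% |
| 1.0 | 1.222 | 0.379 SD | 71.7% |
| 1.5 | 1.500 | 0.420 SD | 62.8% |

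**The case against.** The case on the other side has several parts, and much of it limits the point.

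- **Not an endpoint.** The controls are there for reference values, and the trial's questions are answered within patients. This stands. A reader might infer that the primary result is compromised; it is not, because the SYNTAX and multivessel regressions use patients only and already adjust for age and sex.
- **Not the only powered analysis.** A reader might take the group contrast to be the sole comparison with a power claim. Section 2.9 also claims 80% for MACCE, so that reading fails.
- **Silence in a condensed article.** Figure 1 and part of the text could not be read, and matching may be described in the full protocol. Section 2.1 says that all participants are screened against the criteria, so the 18 to 75 limit may cover controls too. It therefore cannot be said that controls have no age limit or that they will be unmatched, only that no matching is stated. Even a shared 18 to 75 limit would not balance age within that range.
- **The t-test sentence is general.** It is not tied to this contrast. That is so, but no other stated method fits it, and the adjusted model is expressly assigned to other outcomes.
- **Assumed magnitude.** The shifts are assumptions and the resulting range is wide. This stands: the arithmetic shows sensitivity, not the actual bias.
- **No rank test named.** A reader might also fault the lack of a group test for skewed data. That is ordinary analysis-plan detail and is not part of this point.

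**Conclusion.** The point holds as a risk, not as demonstrated confounding. Followed as written, sections 2.2, 2.9 and 2.10 give a powered group comparison with no stated matching or adjustment, and its result could not be attributed to NSTEMI. If covariates alone shift the means by 0.1 to 0.3 SD, the false rejection rate is about 13% to 69% rather than 5%; a shift of 0.05 SD gives 6.9%. These figures rest on assumed shifts, a normal approximation and two-sided 0.05. That the controls will in fact be younger or differ in sex mix is plausible, but the protocol gives no figures for it.

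The matter is of moderate weight: it affects a supporting comparison and the reference values, not the primary or secondary results.

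**What to change.** **Section 2.10.** Compare log(TMAO) and log(TML) between groups by linear regression with group, age and sex as covariates, adding body mass index and renal function where both are collected in both groups. Show the unadjusted t test as descriptive. Section 2.4 collects demographics and risk factors from all individuals, and section 2.7 lists biochemistry at baseline, so little new data should be needed.

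**Section 2.2.** Where controls are still to be recruited, frequency-match them to the study group on sex and age band. The protocol does not say how many controls are already enrolled, so matching supplements the regression and does not replace it.

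**Interpretation.** State that known hypertension and diabetes cannot be adjusted for in this contrast, because controls exclude them by definition. The adjusted difference is therefore still not attributable to NSTEMI alone.

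**Section 2.9.** Restate the power for the adjusted comparison, giving the assumed difference and SD on the log scale. Alternatively, limit the controls to descriptive reference values and drop this power claim, which is the cheaper course.

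**Cost.** One regression per marker, and somewhat slower control recruitment if matching is used. Precision falls as the age gap grows: for an assumed 1 SD gap, power at 0.343 SD drops from 80% to about 72%. Successful matching would avoid most of that loss.

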**Figure 1 F1:**
[figure not shown]
Flow chart diagram of the SZ-NSTEMI study protocol. B/W = between, CAG = coronary angiography, ECG = electrogram, M = month, MACCE = major adverse cardiovascular and cerebrovascular event, MVD = multiple vessels disease, NSTEMI = non ST-segment myocardial infarction, pPCI = primary percutaneous coronary intervention, SVD = single vessel disease, TMAO = trimethylamine N-oxide, TML = trimethyllysine.

Inclusion criteria:

1.Newly diagnosed NSTEMI patients without having previous coronary artery disease2.Having at least single or multiple coronary lesions ≥70% after CAG to fulfill eligibility for pPCI3.Willing to provide informed consent4.Both men and women aged between 18 and 75 years old.

Exclusion criteria

1.Patients with a previous history of coronary artery disease including STEMI, NSTEMI, stable or unstable coronary artery disease or percutaneous transluminal coronary angioplasty or PCI or coronary artery bypass surgery2.Having single coronary lesion < 70% or patient not willing to perform pPCI with single coronary lesion ≥ 70%.3.Having left main coronary artery lesion4.Patients present with diagnosis of STEMI, stable or unstable coronary artery disease5.Patients with severe valvular Heart disease, severe renal and hepatic disease, heart failure, peripheral arterial disease, atrial fibrillation, chronic obstructive lung disease, acute and chronic infection, history of cancer, and history stroke or bleeding within 3 months.6.Patient unwillingness to participate and not willing to provide informed consent7.Pregnancy or lactation8.Conditions related to an estimated life expectancy of less than 1 year.

### Study procedures

2.4

The following information will be obtained from all individuals including baseline demographic, present and past medical history, physical examination findings, 12 lead ECG, and cardiovascular risk factors before enrollment.

Diagnostic CAG and pPCI procedures will be performed by the redial approach within 24 hours of admission under the Fuwai Hospital standard protocol. Multiple diagnostic CAG views will be obtained, for the left anterior descending and left circumflex coronary at least four projections, and the right coronary artery at least two projections. All patients will be received standard oral dual antiplatelet therapy with 300 mg of aspirin (follow by 75–100 mg daily) and 600 mg of clopidogrel (follow by 75 mg daily for ≥ 12 months) as well as intravascular infusions of 70 to 100 IU/kg of unfractionated to weight and boost the operation progressed. During pPCI, the choice and selection of balloons, guide wires, type and size of stents will be determined by the operator.

For primary endpoints, 2 experienced interventional cardiologists blinded to study protocol will evaluate the atherosclerotic burden by the SYNTAX score after the CAG. The SYNTAX score will be calculated from the official SYNTAX score website (www.syntaxscore.com/calculator/syntaxscore/frameset.htm) for each NSTEMI patient. All patients will be divided into two groups according to SYNTAX score including low–intermediate risk (SYNTAX score < 22) and high-risk (SYNTAX score ≥22). The opinion of a third interventional cardiologist will be taken if there is any discrepancy between the results of the SYNTAX score. Moreover, a single vessel disease or multiple vessel diseases will be defined as one or more major coronary vessels exhibiting ≥70% stenosis after the procedure.

### Blood sampling and biomarkers measurement

2.5

Routine and biochemical blood tests will be measured from venous blood samples obtained in a fasting state on the morning following the admission day or before the procedure. An extra EDTA blood sample will also be obtained from each included individual and centrifuged immediately at 2500 g for 10 minutes at room temperature and stored at –80^o^C incubator for later analysis. The plasma TMAO and TML will be measured by isotope dilution high-performance liquid chromatography with online tandem mass spectrometry on an API 3200 triple quadra pole mass spectrometer (AB SCIEX, Framingham, MA) as previously described.^[13–15]^ Laboratory personnel who analyze TMAO, TML and other routine laboratory tests will be blinded to individual characteristics.

### Study outcomes

2.6

The primary endpoint of the study will be assessed an association of TMAO and TML with coronary atherosclerotic severity quantify by the number of diseased coronary arteries, SYNTAX scores after the CAG. For secondary endpoints in Study group, the plasma TMAO and TML will be used as prognostic biomarkers for MACCEs including myocardial infarction, target vessel revascularization, stroke, heart failure, all-cause re-hospitalization and all-cause mortality at the short (1 month) and long-term (12 months) after the pPCI. Each patient in the Study group will be scheduled for follow-up at 1, 3, 6, and 12 months after pPCI at Fuwai hospital by a trained team of cardiologists to identify MACCEs and further clinical consultation.

### Study timeline

2.7

The prospective NSTEMI trial is underway from June 2019 and will be completed in June 2021.

1)Baseline (day 0)Obtain consent documents from each individual.Selection of patients according to inclusion and exclusion criteriaObtain demographic information, present, and past medical history, medication historyRecord results of physical examinations, 12-lead ECG, echocardiographyCollect blood samples (complete blood count, biochemistry, and extra EDTA tube for TMAO and TML biomarkers)Undergo CAG and pPCI (Study Group individuals)2)Short-term (1 month after the pPCI) follow-up visitRecord results of physical examinations, 12-lead ECG, transthoracic echocardiology, present medical history, and consultationShort-term MACCE evaluation3)Long-term (3, 6, and 12 months after the pPCI) visitsRecord results of physical examinations, 12-lead ECG, transthoracic echocardiology, present medical history, and consultationLong-term MACCE evaluation.

